#### 14.3.6 Analysis of the secondary criteria

Descriptive statistics will be performed on secondary endpoints, unless otherwise specified in the statistical analysis plan.

#### 14.3.7 Analysis of exploratory endpoints

Descriptive statistics will be performed, based on the development of a microbiota signature. Results of flow cytometry and multiparameter assay for cytokines will be statistically described to assess the impact of MaaT033 full ecosystem intestinal microbiota biotherapeutic on the immune system.

#### 14.3.8 Interim analyses

No interim analysis is planned.

#### 14.3.9 Sample size justification

Data on safety of MaaT033 in hematologic malignancies are still scarce. As the objective of this study is to assess the safety profile of MaaT033 in patients post intensive chemotherapy for the determination of a recommended phase 2 dose (RP2D), no formal sample size calculation has been made.

21 patients will be allowed estimating various proportions with the following two-sided 95%CI

| Proportion | Two-sided 95%CI |
|------------|-----------------|
| 10%        | [2.1%; 26.5%]   |
| 20%        | [7.7%;38.6%]    |
| 30%        | [14.7%;49.4%]   |
| 40%        | [22.7%;59.4%]   |
| 50%        | [31.3%;68.7%]   |
| 60%        | [40.6%;77.3%]   |
| 70%        | [50.6%;85.3%]   |
| 80%        | [61.4%;92.3%]   |
| 90%        | [73.5%;97.9%]   |

|                                                                                   |                    |                                                                      |
|-----------------------------------------------------------------------------------|--------------------|----------------------------------------------------------------------|
| [figure not shown] | DOCUMENT    | Protocol ID : MPOH05
EudraCT N° : 2019-004253-89
Version: 10.0 |
|                                                                                   | CIMON STUDY | Date : 04 MAY 2021
Page 55 / 70                                   |

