| NUMBER OF SUBJECTS        | 
The enrollment into the study will continue until a maximum of 27 subjects are treated with MaaT033 and evaluable, based on the step-up and safety process:
 
27 patients – 5 cohorts
                                                                                                                                                                                                                                                                                                                                                                                                                                                                                                                                                                                                                                                                                                                                                                                                                                                                                                                                                                                                                                                                                                                                                                                                                                                                                                                                                                                                                                                                                                                                                                                                                                                                                                                                                                                                                                                                                                                                        |

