#### 8.2.2 **Decision rules for choice of dose regimen**

This study has for objective to assess MTD and MAD in term of MaaT033 activity (bacteria engraftment). Activity assessment requires a minimum of 6 patients to allow for a sufficient robust analysis of engraftment.

Activity and tolerability assessment may depend both on duration of treatment and/or daily dose. Therefore, the study will assess both 7 days and 14 days dose regimen, for the 3 capsules/day dosing.

Therefore, the study will ensure that a minimum of 6 patients is included for all the dose regimen that do not reach the MTD.

Definitions:

**Minimal Active Dose (MAD):** Minimum dose regimen that will lead to a minimal activity (1 or 2, cf chapter 8.3.2) of the product.

|                                                                                   |                    |                                                                      |
|-----------------------------------------------------------------------------------|--------------------|----------------------------------------------------------------------|
| [figure not shown] | DOCUMENT    | Protocol ID : MPOH05
EudraCT N° : 2019-004253-89
Version: 10.0 |
|                                                                                   | CIMON STUDY | Date : 04 MAY 2021
Page 24 / 70                                   |

**Dose Limiting Toxicity (DLT):** Toxicity event will be defined as any related adverse event grade >3 based on CTCAE v5.0 criteria for:

- Blood and lymphatic system disorders (DLT when grade4 or 5)
- Immune system disorders (DLT when grade4 or 5)

And any related adverse event grade  $\geq 3$  for all other system organ.

**Maximal Tolerated Dose (MTD):** Maximal dose for which only 0 or 1 patient do experience limiting toxicity out of a cohort of 6 patients.

The study has an adapted “6 dose titration” escalation design to allow for assessment of tolerability (research of the Maximal Tolerated Dose) and of activity (research of Minimal Active Dose):

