### 9.3 **NUMBER OF SUBJECTS PLANNED - REPLACEMENT POLICY**

The enrollment into the study will continue until a maximum of 27 subjects are treated with MaaT033 and evaluable, based on the step-up and safety process.

|                                                                                   |                    |                                                                      |
|-----------------------------------------------------------------------------------|--------------------|----------------------------------------------------------------------|
| [figure not shown] | DOCUMENT    | Protocol ID : MPOH05
EudraCT N° : 2019-004253-89
Version: 10.0 |
|                                                                                   | CIMON STUDY | Date : 04 MAY 2021
Page 27 / 70                                   |

If the compliance is under 60% for a patient, the patient will not be included in the evaluation of the dose-corresponding regimen but will be replaced by another patient.

If a patient becomes positive to SARS-CoV-2 (either nasopharyngeal, oropharyngeal swabs or salivary or other tests or feces tests) during the treatment period, it will be at the investigator's judgment to decide if the patient continues to take the capsules and stay in the study.

In case of COVID-19 pandemic in certain area of the country, an ongoing patient with unmonitored data can be considered to be replaced by another patient in another site in order to validate the corresponding dose regimen by the DSMB.

|                                                                                   |                    |                                                                      |
|-----------------------------------------------------------------------------------|--------------------|----------------------------------------------------------------------|
| [figure not shown] | DOCUMENT    | Protocol ID : MPOH05
EudraCT N° : 2019-004253-89
Version: 10.0 |
|                                                                                   | CIMON STUDY | Date : 04 MAY 2021
Page 28 / 70                                   |

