### 14.1.3 Type 1 error

The analysis will mainly be descriptive. The 1 error rate will be set at 0.05 and therefore two-sided 95% confidence intervals will be calculated.

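### The precision table in Protocol section 14.3.9 is labelled 21 patients but holds exact 95% intervals for 30, a number the protocol nowhere plans

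*Protocol*

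**What the plan says.** Section 14.3.9 states that "no formal sample size calculation has been made". It then offers a precision table instead: "21 patients will be allowed estimating various proportions with the following two-sided 95%CI". The table runs from a proportion of 10%, with interval 2.1-26.5%, through 50%, with 31.3-68.7%, to 90%, with 73.5-97.9%. No interval method is named. Section 14.1.3 fixes the level: "The 1 error rate will be set at 0.05 and therefore two-sided 95% confidence intervals will be calculated".

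The planned number is given elsewhere. Section 9.3 says: "The enrollment into the study will continue until a maximum of 27 subjects are treated with MaaT033 and evaluable". The Synopsis gives "27 patients – 5 cohorts". Section 8.2.2 describes one cohort of 3 and four cohorts of 6, which gives 3 + 4 × 6 = 27.

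**The concern.** Three different sample sizes are attached to one table. The label says 21, the plan says at most 27, and the figures turn out to be those for 30. The proportions themselves are a first hint: 10%, 20%, ..., 90% cannot be observed in 21 patients (2/21 = 9.5%), but each is a whole count in 30.

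What is at stake is how far a reader can trust the stated precision. With no formal sample size calculation, this table is the only place where the protocol says numerically how well a proportion will be estimated. Section 14.1.1 names a proportion of patients with drug-related adverse events as the primary evaluation criterion. An ethics committee or regulator reading the 10% row would take an upper limit of 26.5% as what the trial delivers, and neither 21 nor 27 patients deliver it by that method.

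**Working it through.** **Inputs.** Proportions 10% to 90% and the printed limits (section 14.3.9); two-sided 95% level (section 14.1.3); labelled n = 21 (section 14.3.9); planned maximum n = 27 (section 9.3 and Synopsis).

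**Formula.** For x events in n patients, the exact Clopper-Pearson limits are

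- lower = the 2.5% quantile of Beta(x, n − x + 1)
- upper = the 97.5% quantile of Beta(x + 1, n − x)

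**Step 1: reproduce the printed table.** With n = 30 and x = 3, 6, ..., 27:

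| Proportion | x/30 | Exact 95% CI, n = 30 | Printed |
|---|---|---|---|
| 10% | 3 | 2.1-26.5 | 2.1-26.5 |
| 20% | 6 | 7.7-38.6 | 7.7-38.6 |
| 30% | 9 | 14.7-49.4 | 14.7-49.4 |
| 40% | 12 | 22.7-59.4 | 22.7-59.4 |
| 50% | 15 | 31.3-68.7 | 31.3-68.7 |
| 60% | 18 | 40.6-77.3 | 40.6-77.3 |
| 70% | 21 | 50.6-85.3 | 50.6-85.3 |
| 80% | 24 | 61.4-92.3 | 61.4-92.3 |
| 90% | 27 | 73.5-97.9 | 73.5-97.9 |

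All 18 limits agree to the printed decimal. The neighbouring sizes 29 and 31 miss by about 0.4 points.

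**Step 2: could another method rescue the label 21?** The largest error in any limit at n = 21 is 4.8 points for Wald, 3.0 for Wilson, 5.9 for Wilson with continuity correction, 4.2 for Agresti-Coull, 1.8 for Jeffreys and 4.5 for the exact method. A 90% exact interval at n = 21 does not fit either (at 50% it is 30.7-69.3). None reproduces the table.

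**Step 3: the same method at 21 and 27.** Here x = proportion × n, which is often not a whole number (2.1 of 21, 2.7 of 27). These rows are interpolations for comparison with the table, not results that could be observed. Widths are taken before rounding.

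| Proportion | Printed (width) | n = 21 (width) | n = 27 (width) |
|---|---|---|---|
| 10% | 2.1-26.5 (24.4) | 1.3-31.0 (29.7) | 1.9-27.7 (25.9) |
| 30% | 14.7-49.4 (34.7) | 12.2-53.6 (41.4) | 14.0-50.6 (36.5) |
| 50% | 31.3-68.7 (37.4) | 27.7-72.3 (44.5) | 30.3-69.7 (39.4) |
| 90% | 73.5-97.9 (24.4) | 69.0-98.7 (29.7) | 72.3-98.1 (25.9) |

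Over all nine rows the printed widths fall short by 5.3 to 7.1 points at n = 21, about 16% to 18% of the correct width, and by 1.5 to 2.0 points at n = 27. The largest shift in a single limit is 4.5 points at 21 and 1.2 points at 27.

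**Step 4: attainable counts for 27 patients.** 0/27: 0-12.8%. 3/27: 2.4-29.2%. 5/27: 6.3-38.1%. 8/27: 13.8-50.2%.

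**The case against.** The strongest reply is that the table decides nothing. Section 14.1.3 calls the analysis mainly descriptive, section 14.3.9 claims no formal calculation, and the maximum tolerated dose follows a count rule in section 8.2.2: "Maximal dose for which only 0 or 1 patient do experience limiting toxicity out of a cohort of 6 patients". Against the planned 27 the limits move by about a point. All of this stands, and it limits the weight of the finding without removing it.

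It is also fair that the shortfall depends on the method. A Wilson interval at n = 27 would be slightly narrower than the printed one (at 50%, 32.4-67.6). But Wilson does not produce the printed figures, and the exact method at 30 produces all of them.

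A reader might infer three stronger things that the documents do not support.

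- *That the trial cannot reach 30 patients.* The 27 caps patients who are both treated and evaluable. Under section 9.3, if compliance is below 60%, "the patient will not be included in the evaluation of the dose-corresponding regimen but will be replaced by another patient". The same section allows replacement for COVID-19 reasons, and section 12.1.4.2 lets the cohort review committee add patients. The safety set in section 14.2 counts everyone with at least one capsule intake, so it can exceed 27. What holds is that no section plans 30 and the table says 21.
- *That the table is the sole justification of the sample size.* Section 8.2.2 gives a separate reason for 6 per cohort, the engraftment analysis, and the cohort structure yields the 27. The table is the only quantitative precision statement, not the only rationale.
- *That the table misstates the precision of each regimen's dose-limiting toxicity rate.* It speaks only of proportions in general and makes no claim about single cohorts.

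**Conclusion.** The table is wrong as written. Its label (21), its figures (30) and the plan (27) disagree, and no other section resolves this. By the exact method that generated it, all nine intervals are too narrow, by up to about 4.5 points per limit if 21 was meant and about 1.2 points if 27 was meant. The identification of n = 30 rests on agreement of all 18 limits with the Clopper-Pearson method, since the protocol names none. The comparison figures for 21 and 27 rest on interpolated counts. The effect is modest: no escalation, stopping or maximum-tolerated-dose rule uses the table. It should be corrected because it is a plain error in the only numerical precision statement, not because a decision in the trial would change.

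**What to change.** In section 14.3.9, replace 21 by the planned maximum of 27 treated and evaluable patients and state that the intervals are exact (Clopper-Pearson). Recompute the table at attainable counts and label it as pooled overall safety, for example 0/27: 0-12.8%; 3/27: 2.4-29.2%; 5/27: 6.3-38.1%; 8/27: 13.8-50.2%.

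Optionally, add rows for a single cohort of 6 to show how precisely each cohort's dose-limiting toxicity proportion is known: 0/6: 0-45.9%; 1/6: 0.4-64.1%; 2/6: 4.3-77.7%. This is an addition for the reader, not part of the correction.

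The cost is one sentence and one table. The stated precision becomes slightly less favourable, and no extra patients are needed.

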## **15 ETHICAL AND REGULATORY STANDARDS**

### **15.1 ETHICAL PRINCIPLES**

This Clinical Trial will be conducted in accordance with the principles laid down by the 18th World Medical Assembly (Helsinki, 1964) and all applicable amendments laid down by the World Medical Assemblies, and the International Conference of Harmonization (ICH) guidelines for Good Clinical Practice (GCP).

### **15.2 LAWS AND REGULATIONS**

This Clinical Trial will be conducted in compliance with all international laws and regulations, and national laws and regulations of the country(ies) in which the Clinical Trial is performed, as well as any applicable guidelines.

### **15.3 INFORMED CONSENT**

The Investigator (according to applicable regulatory requirements), or a person designated by the Investigator, and under the Investigator's responsibility, should fully inform the Subject or a Subject's legally acceptable representative of all pertinent aspects of the Clinical Trial including the written information giving approval/favorable opinion by the Ethics Committee (IRB/IEC). All participants should be informed to the fullest extent possible about the study, in language and terms they are able to understand.

Prior to a subject's participation in the Clinical Trial, the written Informed Consent Form should be signed, name filled in and personally dated by the subject or by the subject's legally acceptable representative, and by the person who conducted the informed consent discussion. A copy of the signed and dated written Informed Consent Form will be provided to the subject.

The Informed Consent Form used by the Investigator for obtaining the subject's informed consent must be reviewed and approved by the Sponsor prior to submission to the appropriate Ethics Committee (IRB/IEC) for approval/favorable opinion.

### **15.4 INSTITUTIONAL REVIEW BOARD/INDEPENDENT ETHICS COMMITTEE (IRB/IEC)**

As required by local regulation, the Investigator or the Sponsor must submit this Clinical Trial Protocol to the appropriate Ethics Committee (IRB/IEC), and is required to forward to the respective other party a copy of the written and dated approval/favorable opinion signed by the Chairman with Ethics Committee (IRB/IEC) composition.

The Clinical Trial (study number, Clinical Trial Protocol title and version number), the documents reviewed (Clinical Trial Protocol, Informed Consent Form, Investigator's Brochure, Investigator's CV, etc.) and the date of the review should be clearly stated on the written (IRB/IEC) approval/favorable opinion.

Investigational Product will not be released at the study site and the Investigator will not start the study before the written and dated approval/favorable opinion is received by the Investigator and the Sponsor.

During the Clinical Trial, any amendment or modification to the Clinical Trial Protocol should be submitted to the Ethics Committee (IRB/IEC) before implementation, unless the change is necessary to eliminate an immediate hazard to the subjects, in which case the IRB/IEC should be informed as soon as possible. It

|                                                                                   |                    |                                                                      |
|-----------------------------------------------------------------------------------|--------------------|----------------------------------------------------------------------|
| [figure not shown] | DOCUMENT    | Protocol ID : MPOH05
EudraCT N° : 2019-004253-89
Version: 10.0 |
|                                                                                   | CIMON STUDY | Date : 04 MAY 2021
Page 56 / 70                                   |

should also be informed of any event likely to affect the safety of subjects or the continued conduct of the Clinical Trial, in particular any change in safety.

Updates to the Investigator's Brochure will be sent to the Ethics Committees and Regulatory Authorities for review and approval as required per local country regulations and guidelines (France).

A progress report is sent to the Ethics Committee as required per local country regulations and guidelines (France).

|                                                                                   |                    |                                                                      |
|-----------------------------------------------------------------------------------|--------------------|----------------------------------------------------------------------|
| [figure not shown] | DOCUMENT    | Protocol ID : MPOH05
EudraCT N° : 2019-004253-89
Version: 10.0 |
|                                                                                   | CIMON STUDY | Date : 04 MAY 2021
Page 57 / 70                                   |

## **16 STUDY CONDUCT CONSIDERATIONS**

### **16.1 RESPONSIBILITIES OF THE INVESTIGATOR(S)**

The Investigator(s) undertake(s) to perform the Clinical Trial in accordance with this Clinical Trial Protocol, ICH guidelines for Good Clinical Practice and the applicable regulatory requirements.

The Investigator is required to ensure compliance with all procedures required by the Clinical Trial Protocol and with all study procedures provided by the Sponsor (including security rules). The Investigator agrees to provide reliable data and all information requested by the Clinical Trial Protocol (with the help of the CRF, Discrepancy Resolution Form (DRF) or other appropriate instrument) in an accurate and legible manner according to the instructions provided and to ensure direct access to source documents by Sponsor representatives.

If any circuit includes transfer of data particular attention should be paid to the confidentiality of the subject's data to be transferred.

The Investigator may appoint such other individuals as he/she may deem appropriate as Sub-Investigators to assist in the conduct of the Clinical Trial in accordance with the Clinical Trial Protocol. All Sub-Investigators shall be appointed and listed in a timely manner. The Sub-Investigators will be supervised by and work under the responsibility of the Investigator. The Investigator will provide them with a copy of the Clinical Trial Protocol and all necessary information.

### **16.2 RESPONSIBILITIES OF THE SPONSOR**

The Sponsor of this Clinical Trial is responsible to Health Authorities for taking all reasonable steps to ensure the proper conduct of the Clinical Trial Protocol as regards ethics, Clinical Trial Protocol compliance, and integrity and validity of the data recorded on the Case Report Forms. Thus, the main duty of the Monitoring Team is to help the Investigator and the Sponsor maintain a high level of ethical, scientific, technical and regulatory quality in all aspects of the Clinical Trial.

At regular intervals during the Clinical Trial, the site will be contacted, through monitoring visits, letters or telephone calls, by a representative of the Monitoring Team to review study progress, Investigator and subject compliance with Clinical Trial Protocol requirements and any emergent problems. These monitoring visits, will include but not be limited to review of the following aspects: subject informed consent, subject recruitment and follow-up, Serious Adverse Event documentation and reporting, AE documentation, Investigational Product allocation, subject compliance with the Investigational Product regimen, Investigational Product accountability, concomitant therapy use and quality of data.

### **16.3 SOURCE DOCUMENT REQUIREMENTS**

According to the ICH guidelines for Good Clinical Practice, the Monitoring Team must check the Case Report Form entries against the source documents, except for the pre-identified source data directly recorded in the Case Report Form. The Informed Consent Form will include a statement by which the subject allows the Sponsor's duly authorized personnel and the regulatory authorities to have direct access to original medical records which support the data on the Case Report Forms (e.g., subject's medical file, appointment books, original laboratory records, etc.). These personnel, bound by professional secrecy, must maintain the confidentiality of all personal identity or personal medical information (according to confidentiality rules).

Subject's identification details, medical history, associated diseases, data related to the studied pathology, previous and concomitant medications, a statement that the informed consent was signed by the subject,

|                                                                                   |                    |                                                                      |
|-----------------------------------------------------------------------------------|--------------------|----------------------------------------------------------------------|
| [figure not shown] | DOCUMENT    | Protocol ID : MPOH05
EudraCT N° : 2019-004253-89
Version: 10.0 |
|                                                                                   | CIMON STUDY | Date : 04 MAY 2021
Page 58 / 70                                   |

study identification (name), dates of study visits, treatment number, dates of administration of IP, examinations and assessments carried out at each visit, adverse events (+ follow-up), date of study discontinuation (if any) and reason.

Source documentation must include the faxed Central lab reports (dated and signed by the Principal Investigator or Sub-Investigator), the screening, screen failure, discontinuation, and end of study).

In case of SAE, the site should file in the source document at least copies of the hospitalization reports and any relevant examination reports documenting the follow-up of the SAE.

NOTE: Patient's involvement in the study should be clearly documented in his/her medical file; details should include the study protocol number, the hospital/unit code, the patient's identification and enrollment number, the patient's consent/assent to take part in the study (with the date of consent/assent), the dates of all study visits. Such essential documents must be retained by the Investigator in accordance with local regulations.

|                                                                                   |                    |                                                                      |
|-----------------------------------------------------------------------------------|--------------------|----------------------------------------------------------------------|
| [figure not shown] | DOCUMENT    | Protocol ID : MPOH05
EudraCT N° : 2019-004253-89
Version: 10.0 |
|                                                                                   | CIMON STUDY | Date : 04 MAY 2021
Page 59 / 70                                   |

